#### Aim 2: To determine how affordability, accessibility, and awareness (3As) affect sustained use of LPG in adopter households

We will conduct two types of analyses:We will analyze the usage pattern data (using SUMS data log sheet) from LPG stoves and traditional stoves for the monitoring period of 12 months. This trend of usage pattern (without any covariates) will be analyzed for the monitoring period of 12 months using R version 3.0.3.The households will be dichotomized into exclusive LPG users and stackers depending on their usage pattern. Households using LPG at least 80% of the cooking duration during the monitoring period of 12 months will be characterized as exclusive LPG users. The dichotomous outcome will then be regressed on the 3As data from follow up questionnaire data. Preliminary univariate and bivariate data analyses will precede regression analyses. We will use R version 3.0.3 for analyses.

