### Study participants (*N* = 510; 255 from each group)

The inclusion criteria for the study participants are: rural household with an adult male and female member (>18 years age), woman respondent who is able to provide consent for the study, the woman respondent is the primary cook of the house, senior most male respondent (or primary male decision maker in the household) who is able to provide consent for the study, women respondent residing in the household for the last 12 months, women respondent plans to reside in the household for at least 12 months from the date of enrollment for the study. An additional inclusion criterion for case group (LPG adopter households) is: household has received the first LPG cylinder in the last 12 months from the date of enrollment for the study.

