### Data collection

#### Aim 1: To understand how rural LPG adopters vary from other rural households on factors of affordability, accessibility, and awareness of LPG

A structured household adoption questionnaire will be used to record data on social, economic, and demographic characteristics. Women (primary cook) from each household will be the respondent for this questionnaire. In addition to household demographic characteristics, the questionnaire will record data pertaining to the 3 significant drivers impacting LPG adoption: affordability, accessibility, and awareness (3As) of LPG. The categorical outcome variable for aim 1 will be adoption of LPG at the time when data collection is undertaken for the household. Candidate variables on affordability include household income, upfront costs to acquire LPG, access to bank loans, facility of payment in installments for LPG purchase and refill, regularity of income (in past 12 months), and women’s financial autonomy. Candidate variables on accessibility include distance of habitations and households from LPG distribution centers, presence of paved roads to LPG distribution centers, and nature of LPG cylinders’ home delivery system. Candidate variables for awareness include government promotion campaigns, local self-government *(Gram Sabha)* awareness drives, and participation of women in self-help groups. In addition, we will capture data on how organizations at the community level, including government entities, and LPG distributors shape household adoption and sustained use of LPG. Candidate organizational factors are irregular supply and bureaucratic hurdles to apply for LPG, which will be assessed from the perspective of households. Key control variables that will be recorded are caste, household size, months of LPG ownership (in case group), educational status of household head, and free availability of biomass. This adoption questionnaire for aim 1 will be administered to all 510 households immediately after their enrollment in the study.

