#### Aim 2: To determine how affordability, accessibility, and awareness affect sustained use of LPG in adopter households

To study sustained use, we will focus on group 1 (LPG adopters) of our sample. SUMS will be used to measure duration of use (a measure of maintenance) of clean cooking technologies of the study participants. We will use SUMS for both the LPG stoves and traditional cookstoves in a randomly selected subset of 100 households from group 1 (LPG adopters) [31]. We will receive SUMS data on: 1) duration of use of these stoves; 2) extent of use of LPG stoves relative to traditional stoves. We will monitor the use of these stoves for 12 months. SUMS data will be recorded and downloaded every two weeks from each of the 100 households by a trained field person. We will download data using a probe connected to a laptop computer via USB port. Files will be uploaded to our database management system (RedCap). Informed consent will be obtained from the households to continue using the stoves as they do routinely. SUMS will provide continuous data on stove usage in 100 households. For analysis purposes, we will also dichotomize this data as: 1) exclusive LPG users, and 2) stackers. Households using LPG at least 80% of the cooking duration during the monitoring period of 12 months will be characterized as exclusive LPG users. This metric will facilitate comparison of the results of this study with other LPG adoption studies currently underway in different parts of the world [32]. We will use a SUMS data log sheet to record the biweekly SUMS data on sustained use. In addition, we will undertake a follow up survey in these 100 households. During the monitoring period (post enrollment of households) status of 3As in the habitations might change. This requires a follow up survey at the end of 6 and 12 months of the monitoring period. Follow up survey will have questions pertaining to the 3As, focused on the monitoring period. Follow up questionnaires and SUMS data collection will be administered to 100 LPG adopter households.

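### Aim 2 follows households that start at different points in their first year of LPG ownership, but its usage trend has no covariates and its regression names only the 3As

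*Protocol article*

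**What the plan says.** All references are to the protocol article.

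- **Study participants.** The extra criterion for adopters is: "household has received the first LPG cylinder in the last 12 months from the date of enrollment for the study".
- **Data collection, aim 1.** The list of controls reads: "Key control variables that will be recorded are caste, household size, months of LPG ownership (in case group"), followed by education of the household head and free availability of biomass.
- **Data collection, aim 2.** Sensors are placed "in a randomly selected subset of 100 households from group 1 (LPG adopters"), with no restriction on ownership time. The duration is stated as: "We will monitor the use of these stoves for 12 months". Monitoring follows enrolment; no calendar start is given.
- **Data analysis, aim 2.** First analysis: "This trend of usage pattern (without any covariates) will be analyzed for the monitoring period of 12 months". Second analysis: households are split at 80% LPG share of cooking time over the 12 months, and then "The dichotomous outcome will then be regressed on the 3As data from follow up questionnaire data".

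The limitations section does not mention ownership time or season.

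**The concern.** The same 12 monitoring months cover different parts of the ownership history in different households. Two consequences follow.

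1. **Trend.** This is the only aim 2 analysis described that does not first dichotomise the sensor data. With one year of data and no covariates, a rise or fall over monitoring months may reflect time since adoption, season, or both.
2. **Regression.** Ownership time could plausibly change both LPG share and the answers on awareness or access, for example through experience with refills. If so, leaving it out confounds the 3A estimates.

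The RE-AIM section reads these sensor data as maintenance. The limitations section says the study will supply effect sizes for a larger study, so a distorted estimate would carry forward.

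**Working it through.** **Stated figure.** The article gives no figure for aim 2. Its only sample size concerns income in aim 1, and it reproduces: 2 × (1.96 + 0.842)² × (2199.26 / 545.35)² ≈ 255 per group at 80% power. Nothing below depends on it.

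**Step 1: ownership windows.** Let u be months of ownership at the start of monitoring, taken as enrolment. Then u runs from 0 to 12 and the window is u to u + 12.
- u = 0 gives ownership months 0–12.
- u = 12 gives ownership months 12–24.

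If u is uniform (an assumption), two random households differ by 12/3 = 4 months on average, so they share 12 − 4 = 8 of 12 ownership months. A common delay between enrolment and monitoring moves the range later but does not narrow it.

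**Step 2: where recorded ownership can be used.** It has no value for non-adopters, so it cannot adjust the aim 1 comparison of adopters with non-adopters. Aim 2 contains adopters only, so it can be used there.

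**Step 3: season and the 80% label.** Each 12-month window holds every calendar month once. The mean of a stable annual sine over 12 months is 0 for all 12 start months. Season therefore does not distort the label through start date.

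**Step 4: season and the trend.** If all households start together, monitoring month is calendar month. Suppose a straight line is fitted to 12 monthly values.
- Sum of squares of month: 12 × (144 − 1)/12 = 143.
- Largest slope of an annual sine, per unit amplitude: [12 / (2 sin 15°)] / 143 = 0.162 per month.
- With an assumed swing of ±10 points: 1.62 points per month, or 1.62 × 11 ≈ 18 points from month 1 to month 12.

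This is the worst start season. Staggered starts blend calendar months and would reduce it.

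**Step 5: regression, illustration A.** All inputs are assumed: u uniform on 0–12, between-household SD 1 logit, typical LPG share 70% at ownership month 12, and a 3A variable with no true effect whose correlation with ownership is 0.3 to 0.5.

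| Drift in LPG share (logit per ownership month) | Exclusive users, u < 3 | Exclusive users, u > 9 | OR per SD without ownership (correlation 0.3; 0.5) |
|---|---|---|---|
| −0.10 | 45% | 15% | 0.85; 0.75 |
| −0.05 | 37% | 22% | 0.93; 0.87 |
| 0 | 30% | 30% | about 1.0 |
| +0.05 | 22% | 37% | 1.08; 1.16 |
| +0.10 | 15% | 45% | 1.19; 1.31 |

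With ownership in the model, every odds ratio is about 1.0 (0.98 to 1.02).

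**Illustration B**, at n = 100, assumes an LPG share SD of 15 points, a fall of 1 to 2 points per ownership month and the same correlations. The median odds ratio without ownership is 0.88 to 0.69, with rejection in 8% to 39% of runs at the 5% level. With ownership it is about 1.0, with rejection in 4% to 5%.

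**Step 6: can ownership and season be separated?** Ownership month equals u plus monitoring month. With a common start, calendar-month terms absorb monitoring month, so the ownership slope rests only on differences in u between households. With a fixed household effect it would not be identified. With a share SD of 15 points and u uniform (SD 12/√12 = 3.46), the standard error of that slope is about 15 / (3.46 × √100) = 0.43 points per month.

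**The case against.** The strongest reply is that this is a condensed article describing an exploratory study. The regression omits ownership only by silence. Aim 1's analysis section does not list its full adjustment set either, and a variable called a key control that exists only for adopters may well be meant for aim 2. That stands: a reader might infer that the regression excludes ownership by decision, and the text does not say so. It does not rescue the trend, where the absence of covariates is stated.

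Other tempting readings also go too far.

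- **Early monitoring is uptake, not use.** The article defines adoption as a yes/no household status, independent of later use. Every monitored household has adopted, so what varies is the stage of ownership. The definitions are not contradicted.
- **Season biases the 80% classification.** It does not (step 3).
- **The bias is known to be large, or to run one way.** Its sign reverses with the direction of drift. At the mild end of illustration B, rejection is 8% against a nominal 5%.
- **The trend analysis will give a false slope.** The article specifies no line or test. A plain monthly curve would show a seasonal pattern, though it could not say whether season or ownership caused it.

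A further objection concerns the remedy. In the article's own model the 3As foster adoption, so better-placed households may adopt earlier. Adjusting for ownership could then remove part of a real effect of distance or income. That stands, and it is why both estimates should be reported.

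**Conclusion.** The concern holds in limited form. Entry at 0–12 months of ownership and a trend without covariates are both in the text. Together they mean that the trend mixes ownership stages and cannot distinguish time since adoption from season. For the regression, the point is that a recorded variable usable only among adopters is not placed in the one analysis where it could act as a control.

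Size and direction cannot be read from the documents. The odds ratios of 0.75 to 1.31 (A) and 0.88 to 0.69 (B) require both a drift in LPG share with ownership and a 3A variable correlated with ownership. Without either, there is no bias. The figure of 1.6 points per month requires a ±10-point season, a common start, a fitted line and the worst start season. Because aim 2 is exploratory, this is an improvement worth making to the analysis; it does not invalidate the study.

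**What to change.** In Data analysis, aim 2:

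1. Remove the restriction to a trend without covariates. Show usage by calendar month and by months since first cylinder. Model it with both time scales and a random household effect.
2. State that the ownership slope rests on contrasts between households (wholly so if all start together), and that it assumes earlier and later adopters do not otherwise differ.
3. Add months of ownership at enrolment to the regression of exclusive use on the 3As. Report estimates with and without it, because stable 3As may influence when a household adopts.

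**Cost.** No new data, since ownership is already recorded. The regression loses one degree of freedom among 100 households. Calendar-month terms take up to 12 − 1 = 11 degrees of freedom in the trend model, and the ownership slope will be less precise than a simple slope on monitoring month.

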*Sustained use* shows the degree to which LPG is used and has been integrated in daily behavior of users [29, 30]. Sustained users who exclusively use LPG make a complete switch to LPG with no intention of reverting to traditional stoves or traditional fuels [29]. Stackers are those households who combine use of LPG with traditional stoves. We study the degree of use of each of these stoves for a select number of households (from group: LPG adopters) by using the Stove Use Monitor Systems (SUMS) technology. SUMS are based on commercially available temperature loggers, which record the variation in the stove temperature over a defined period of time to provide accurate insights into stove usage patterns, duration of use, and number of meals cooked. There are numerous models of SUMS available. For this study we are using iSUMS model DS 1922 L, which can record data for as long as 4–6 weeks post installation on the stoves [31]. Sustained use of LPG is a continuous outcome variable (aim 2). We measure this variable with the help of SUMS technologies, which will record the number of hours of use of LPG stoves and of traditional stoves. For analysis, we can also dichotomize sustained use into two categories: exclusive LPG users, and stackers. Households which use LPG at least 80% of the total cooking duration during our monitoring period (recorded with SUMS technology) will be characterized as exclusive LPG users. Such a metric will allow us to compare the results of this study with other LPG adoption studies now underway in different parts of the world [32];

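### Aim 2 declares sustained LPG use a continuous outcome, but only the 80% yes/no version is modelled on the 3As, so the declared outcome is never related to its determinants

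*Protocol article*

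**What the plan says.** Among the definitions under Study design, the article states: "Sustained use of LPG is a continuous outcome variable (aim 2"). The sensors record hours of use of the LPG stove and of the traditional stoves. The cut is then offered as an extra: "For analysis, we can also dichotomize sustained use into two categories: exclusive LPG users, and stackers". Data collection, Aim 2, repeats this: "For analysis purposes, we will also dichotomize this data as: 1) exclusive LPG users, and 2) stackers".

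Data analysis, Aim 2, announces two types of analysis. Of the first it says: "This trend of usage pattern (without any covariates) will be analyzed for the monitoring period of 12 months". The second starts from the cut, "Households using LPG at least 80% of the cooking duration during the monitoring period of 12 months will be characterized as exclusive LPG users", and continues: "The dichotomous outcome will then be regressed on the 3As data from follow up questionnaire data".

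The 3As for this model come from surveys in the same 100 households: "This requires a follow up survey at the end of 6 and 12 months of the monitoring period".

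Study aim words Aim 2 as covering both sustained and exclusive use. The Aim 2 headings under Data collection and Data analysis mention sustained use only.

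**The concern.** Aim 2 asks how the 3As affect use of LPG after adoption. The analysis that uses the continuous sensor data contains no 3As, and the analysis that contains the 3As does not use the continuous data. As written, the declared outcome is never regressed on the predictors that the aim names.

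Two things are at stake. First, a household at 79% LPG and one at 5% are treated alike, as are one at 81% and one at 100%, so any 3A effect within either class is invisible. Second, the sample is only 100 households, and the Limitations section itself calls that small. It names the loss of multilevel modelling as the consequence, but not the information given up by the cut. The study is also meant to supply effect sizes for a larger study, and an inefficient model makes those less precise.

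**Working it through.** **Reading the two analyses against the aim**

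| Part of Aim 2 (Study aim) | Outcome form | Analysis given | 3As in the model? |
|---|---|---|---|
| Sustained use | Continuous (Study design) | Trend over 12 months | No |
| Exclusive use | At least 80% LPG, yes/no | Regression | Yes |

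The Limitations section speaks of regressing sustained use (sensor data) on the 3As in 100 households, but does not say that the continuous form is used. It does not fill the empty cell.

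**The plan's own power figure**

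The only sample-size statement concerns monthly income, cases against controls: difference 545.35 INR, SD 2199.26 INR, two-sided alpha 0.05, power 80%.

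n per group = 2 × (1.96 + 0.84)² × (2199.26/545.35)² ≈ 2 × 7.85 × 16.26 ≈ 255.3, so 256 after rounding up. At 255 per group, power is 79.95% (79.8% by the noncentral t). The stated figure reproduces, but it says nothing about the 100 households of Aim 2.

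**Information kept by the cut**

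Assumptions not in the document: the LPG share is normal on some scale, and a proportion p of households lies on one side of the cut. The efficiency relative to the continuous outcome is φ(z_p)² / [p(1−p)], where φ is the normal density at the cut.

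- p = 0.5: 0.399² / 0.25 = 0.64
- p = 0.2: 0.280² / 0.16 = 0.49
- p = 0.1: 0.175² / 0.09 = 0.34

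For this purpose the 100 households are worth about 64, 49 or 34.

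**What this does to power**

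Take a predictor with 80% power on the continuous outcome at n = 100. By Fisher's transformation its correlation is tanh(2.80/√97) ≈ 0.28. After the cut, power ≈ Φ(2.80 × √efficiency − 1.96). The simulation used 3000 runs per split, one normal predictor and a logistic likelihood-ratio test.

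| Assumed split | Information kept | Power, formula | Power, simulation |
|---|---|---|---|
| 50/50 | 64% | 61% | 64% |
| 20/80 | 49% | 50% | 52% |
| 10/90 | 34% | 37% | 38% |

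**Sensitivity to the shape of the shares**

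Let shares pile up near 0% and 100% (logistic transform of a normal with SD 5, an assumption) with a 50/50 split. A linear model of the share then has about 72% power, against 60–62% after the cut. Power of 72% corresponds to 1.96 + 0.58 = 2.54. Powers of 60% and 62% correspond to 2.21 and 2.27. The information kept is (2.21/2.54)² = 0.76 to (2.27/2.54)² = 0.80, a loss of a fifth to a quarter rather than 36%.

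**The case against.** The strongest defence is that exclusive use is itself part of Aim 2 and that the 80% threshold has a stated reason, comparability with other LPG studies. The Background also argues that health benefit needs very low exposure, which favours a high threshold. This stands: the binary regression answers a stated question and should stay. It does not supply the missing model for sustained use. The description of the study as exploratory softens the consequence but does not remove the mismatch.

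A reader might infer several stronger criticisms, which the documents do not support.

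- **A fixed loss of a third to two thirds.** The article gives neither the split nor the distribution, and the loss can be smaller, as shown above.
- **An overfitted model with too few events per variable.** The twelve candidate variables one can count are listed for the Aim 1 adoption questionnaire. The items of the follow-up survey are not listed, the number of exclusive users is unknown, and nothing says that all candidates enter one model.
- **Reverse causation because the month-12 survey comes after the outcome.** Data collection says that the follow-up questions concern the monitoring period, so the survey looks back over the time in which use accrued. The Limitations section discloses the resulting recall bias.
- **A misused label.** The text says "Stackers are those households who combine use of LPG with traditional stoves", so a household at 85% LPG fits both descriptions. But the 80% rule is stated openly each time with its threshold, so this is mainly terminology.

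**Conclusion.** The point holds as an internal inconsistency with a cost in efficiency. Sustained use is declared continuous and the cut is described as additional, yet the only 3A regression for Aim 2 uses the cut. The gap is the missing continuous regression; the binary one is not wrong.

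Under a latent-normal share, the cut keeps 64%, 49% or 34% of the information at 50/50, 20/80 or 10/90 splits, and power falls from 80% to about 61–64%, 50–52% or 37–38%. These are conditional figures. More extreme splits cost more, and shares piled up at both ends cost less. That the declared outcome has no 3A model depends on none of these assumptions.

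**What to change.** In Data analysis, Aim 2, add a regression of each household's LPG share of total cooking time on the 3As, and name it the main analysis of sustained use. A fractional logit or a beta regression would serve; the fractional logit copes directly with shares of exactly 0 or 1. Pair each follow-up survey with the interval it covers: the month-6 survey with months 0–6, and the month-12 survey with months 6–12. Allow for the two intervals within a household by household-clustered standard errors or a random effect. The month-12 questions should refer to the time since the month-6 survey, so that the pairing is exact.

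Pairing the month-6 survey with months 6–12 instead would match that interval to answers about the preceding one and leave the month-12 survey unused.

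Keep the 80% regression alongside as the exclusive-use analysis and for comparison with other studies.

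The cost is small. The two-weekly sensor downloads and both surveys are already planned. It takes a little more analysis, and coefficients on the share scale will need explaining next to the 80% category.
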